## Abstract

**Background:**

In recent years, a growing body of literature has highlighted the role of wearable and mobile remote measurement technology (RMT) applied to seizure detection in hospital settings, whereas more limited evidence has been produced in the community setting. In clinical practice, seizure assessment typically relies on self-report, which is known to be highly unreliable. Moreover, most people with epilepsy self-identify factors that lead to increased seizure likelihood, including mood, behavior, sleep pattern, and cognitive alterations, all of which are amenable to measurement via multiparametric RMT.

**Objective:**

The primary aim of this multicenter prospective cohort study is to assess the usability, feasibility, and acceptability of RMT in the community setting. In addition, this study aims to determine whether multiparametric RMT collected in populations with epilepsy can prospectively estimate variations in seizure occurrence and other outcomes, including seizure frequency, quality of life, and comorbidities.

**Methods:**

People with a diagnosis of pharmacoresistant epilepsy will be recruited in London, United Kingdom, and Freiburg, Germany. Participants will be asked to wear a wrist-worn device and download ad hoc apps developed on their smartphones. The apps will be used to collect data related to sleep, physical activity, stress, mood, social interaction, speech patterns, and cognitive function, both passively from existing smartphone sensors (passive remote measurement technology [pRMT]) and actively via questionnaires, tasks, and assessments (active remote measurement technology [aRMT]). Data will be collected continuously for 6 months and streamed to the Remote Assessment of Disease and Relapse-base (RADAR-base) server.

**Results:**

The RADAR Central Nervous System project received funding in 2015 from the Innovative Medicines Initiative 2 Joint Undertaking under Grant Agreement No. 115902. This Joint Undertaking receives support from the European Union’s Horizon 2020 research and innovation program and European Federation of Pharmaceutical Industries and Associations. Ethical approval was obtained in London from the Bromley Research Ethics Committee (research ethics committee reference: 19/LO/1884) in January 2020. The first participant was enrolled on September 30, 2020. Data will be collected until September 30, 2021. The results are expected to be published at the beginning of 2022.

**Conclusions:**

RADAR Epilepsy aims at developing a framework of continuous data collection intended to identify ictal and preictal states through the use of aRMT and pRMT in the real-life environment. The study was specifically designed to evaluate the clinical usefulness of the data collected via new technologies and compliance, technology acceptability, and usability for patients. These are key aspects to successful adoption and implementation of RMT as a new way to measure and manage long-term disorders.

**International Registered Report Identifier (IRRID):**

PRR1-10.2196/21840

## Introduction

### Background

The last decade has seen an explosion in the capability of monitoring individuals via sensors in smartphones or wearable devices, and the range of parameters that can be measured by such technologies will continue to grow [1]. Remote measurement technologies (RMTs) can unobtrusively measure human behavior and physiology and, combined with active measurement of daily experiences via smartphone apps, is an innovation that could be used to provide real-time information about the current clinical state of patients and information potentially predictive of future deterioration [1]. RMT appears to be particularly interesting for those chronic conditions whose course is dynamic and characterized by multiple variations in parameters that can be measured remotely, actively and/or passively [2,3]. Epilepsy is one of the most common neurological disorders, affecting approximately 0.6% of the population worldwide [4]. It is characterized by recurrent seizures that manifest with physiological and behavioral phenomena [5]. Seizures are mostly unprovoked and unpredictable, and about 1 in 3 of all people with epilepsy do not respond to any medication and continue to have uncontrolled seizures [6]. The personal, social, and economic costs of uncontrolled epilepsy are considerable: seizure recurrence and unpredictability worsen the quality of life (QoL) of people with epilepsy and their families [7], people with active epilepsy have 4 to 5 times higher standardized mortality ratios compared with seizure-free individuals [8-12], and the economic burden for the health system is significant across countries [13,14]. Despite new antiepileptic drugs coming to the market, there is limited evidence of a substantial difference to treatment-refractory patients [15], and overall, the mortality associated with epilepsy has not decreased in the last 50 years [16]. One reason for the failure of trials of new treatments is that it is difficult to collect objective data regarding relevant clinical outcomes (eg, number of seizures and response to treatment) and that subjective patient and family recall and reporting is of limited utility and largely unreliable [17]. Similarly, an objective and continuous collection of information on seizure occurrence, frequency, and distribution would guide a more tailored management and inform decisions on treatment optimization in the clinical setting. In the diagnostic setting, the gold standard for seizure detection is electroencephalography (EEG) in combination with video monitoring. This method has, by definition, a high sensitivity and a positive predictive value close to 100%. However, video EEG monitoring is not a practical procedure for long-term seizure tracking for different reasons: it cannot be implemented for more than a few days at a time, wearing EEG electrodes is uncomfortable and potentially stigmatizing for the patient, EEG requires considerable care by technicians to maintain a high signal quality, and analysis of videos and EEG signals are time consuming and costly [18].

The advent of small, wearable sensors embedded in devices and smartphones has progressively attracted attention in the epilepsy research field [19]. Wearable sensors can be worn comfortably for continuous monitoring of biosignals, and no input from the wearer is required to gather data (passive remote measurement technology [pRMT]). Different studies, mostly based on epilepsy monitoring units (EMUs), have demonstrated the possibility of capturing cardinal seizure manifestations using wearable sensors [20-26]. Movements presenting during seizures have been recorded with accelerometry and surface electromyography. Heart rate variations have been captured by wearable electrocardiogram (ECG) and photoplethysmography (PPG), and alteration of the autonomic nervous system has been recorded with ECG, PPG, and electrodermal activity (EDA) sensors, with different levels of signal and seizure detection accuracy [27].

However, although seizures are the hallmark of the condition, most people with epilepy also develop a range of comorbid conditions of variable severity, including mood disturbances and memory impairment, which are strong predictors of QoL [28]. Moreover, the majority of people with epilepsy self-identify seizure precipitants, usually identified as social and behavioral factors, such as stress, sleep deprivation, and fatigue, which lead to increased seizure likelihood [29]. Despite their clinical importance, there is limited evidence regarding the temporal trajectory of cognitive and psychiatric comorbidity of epilepsy, and insufficient studies have prospectively evaluated the correlation between seizure precipitants and seizure occurrence.

RMT provides tools to reliably measure mood states, cognition, thoughts, and behaviors in real time [30-32], with evidence highlighting the increased validity of this methodology in comparison with traditional retrospective reports [33]. Smartphone apps can be used to deliver validated questionnaires, cognitive games, speech tasks, or electronic diaries to provide fine-grained understanding of mood changes and stressors in the context of daily life (active remote measurement technology [aRMT]) [34]. Moreover, information gathered through smartphones, including GPS, communication logs, ambient noise, light levels, and screen interactions, has been successfully used to identify changes in sleep and activity patterns in psychiatric conditions [35,36] and represent an additional pRMT feature. Despite the growing body of research evidence, there has been limited assessment of the utility of multiparametric RMTs (aRMT and pRMT) in specific clinical populations, and a paucity of studies performed in the context of daily life have used wearables for people with epilepsy [25]. Remote Assessment of Disease and Relapse-Central Nervous System (RADAR-CNS) is an international research program, which has developed an open-source platform to support pRMT and aRMT data collection to assess and monitor 3 different clinical conditions, major depressive disorder [37], epilepsy, and multiple sclerosis, in the ambulatory setting.

This study reports the methods of a clinical study, RADAR Epilepsy, designed to test patients’ acceptability and the clinical utility of multiparametric RMT in a clinical population with epilepsy in the real-world environment.

### Study Development and Patients’ Involvement

Systematic reviews have examined the barriers and facilitators of RMT uptake [38]; surveys and service user focus groups have identified device preferences and the variables of interest to the specific patient group [39,40]. Alongside clinical experts, the RADAR-CNS consortium has a team dedicated to ensuring patient and public involvement at every stage of development. People with epilepsy took part in focus groups to gather their views on the outcomes of importance to patients and potential barriers and facilitators to engagement [40]. We have appointed several people with epilepsy, in collaboration with a national charity (Epilepsy Action), to join a patient advisory board to help steer the project. These members and people with epilepsy in a hospital-based setting were involved in user testing the wearable devices and smartphone apps, contributing to crucial design choices throughout [40]. All information sheets have been reviewed and approved by a local service user advisory board (Feasibility and Acceptability Support Team for Researchers) and patients seen in local epilepsy clinics to ensure their accessibility. We will continue to involve patients throughout this study and include them in the dissemination of research findings.

### Study Objectives

The main aims of the RADAR Epilepsy study are (1) to determine the usability and acceptability of RMT to provide real-time objective multidimensional indications of clinical state in individuals with epilepsy; (2) to assess the correspondence of patient-marked seizure events (via aRMT) with the data collected from the pRMT; and (3) To determine whether multiparametric RMT collected in populations with epilepsy can prospectively estimate variations in seizure occurrence and other outcomes, including seizure frequency, QoL, and comorbidities.

## Methods

### Study Design and Population

This study is a multicenter, prospective, observational, nonrandomized, and noninterventional cohort study in which 32 individuals with a diagnosis of epilepsy will be asked to download several RMT apps and use a wearable device for up to 6 months of follow-up. The inclusion and exclusion criteria are provided in Textboxes 1 and 2, respectively.

Inclusion criteria.Inclusion criteriaAble to give informed consent for participationDiagnosis of epilepsyAged between 18 and 70 yearsMinimum average seizure frequency of 2 seizures per monthWilling and able to complete self-reported assessments via smartphonesFluent in English (German in Freiburg) and able to read and write English (German in Freiburg)Willing to continuously wear the study wearable deviceExisting ownership of an Android smartphone (or willingness to use an Android smartphone, which will be provided as their only smartphone)Existing ownership or the possibility of connecting to a Wi-Fi connection on a daily basis

Exclusion criteria.Exclusion criteriaEstablished diagnosis of psychogenic nonepileptic attacks (dissociative seizures) as the only seizure typeFrequent vigorous involuntary movements (eg, chorea and athetosis) or frequent parasomnias with major motor components (eg, sleep walking and night terrors)Inability to comply with the trial procedure, such as cognitive or behavioral problemsInability to give informed consentUnwillingness to use an Android smartphone

### Study Technology

The open-source RADAR-base platform [41] developed to support the RMT data collection is described elsewhere [42]. A number of variables will be collected from each patient through the RMT.

pRMT includes the following:

Smartphone app: Participants will be assisted in downloading a purpose-built app that will run in the background, requiring no further input. Using sensors commonly present in all modern smartphones, the app will collect data on ambient noise, ambient light, GPS location, bluetooth connectivity, and battery life. GPS location data will be randomized (providing relative location data, not absolute coordinates).Wearable device: Participants will be asked to wear the Empatica E4 device, a Conformitè Europëenne–marked wristband (Figure 1), for the entire duration of the study (6 months). The device will require a few hours of charging once daily, and participants will receive training and accessories to do so on a routine basis and a second E4 device to be worn during the charging procedure. The sensors included in this wearable device and the parameters measured are PPG and series of interbeat intervals derived from it, 3D acceleration, body temperature, and EDA.

A number of variables of interest to this study will be collected through a second purpose-built aRMT app, which will prompt the study participant to complete validated questionnaires and assessments according to the study schedule (Table 1):

Psychiatric comorbidities: Anxiety will be measured via the 7-item Generalized Anxiety Disorder Questionnaire [43]; depressive symptoms will be monitored via the 8-item Patient Health Questionnaire [44].
Seizure occurrence and precipitants: Each evening, participants will be prompted to complete a daily assessment to provide self-reported information about medication compliance, sleep quality, alcohol use, menstrual cycle, stress, mood, anxiety, and seizure occurrence. If a seizure is reported, the participant will be automatically directed to an ad hoc created seizure diary. Information on clinical symptoms and manifestations, time of the event, and possible precipitants will be collected through the diary.Experience sampling method: Participants will be asked to complete a series of short electronic diary assessments, also known as the experience sampling method (ESM). ESM assesses experiences and behavior in the realm of daily life and will be administered to provide real-time self-reported data on mood, stress, cognition, activity, location, social interactions, physical state, and medication use. An ESM period will be initiated once every 6 weeks, during which participants will receive notifications to complete 9 questionnaires per day over a 6-day period (semirandom interval between 8:30 AM and 10 PM).
Speech task: On a random schedule, participants will be asked to hold down a button on their phone to start recording and will then be asked to say aloud, and in a quiet area, some excerpts from *The North Wind and the Sun*, which are shown to be phonetically balanced in different languages. In addition, participants will be asked to respond to the following question: *Can you describe something you are looking forward to this week?* These data will be recorded in a raw audio format, allowing speech recognition to extract content and automatic sentiment detection.Cognitive function: Cognitive assessment will use the THINC-ITapp, which has been validated to screen for cognitive dysfunction [45] and examines executive functions, such as memory, attention, and concentration.

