**Active** **RMT**														
	Seizure diary and precipitants	—	—	—	—	—	—	Daily questionnaire	—	—	—	—	—	—
	ESM^f^ assessment	✓	—	—	✓	—	—	✓	—	—	✓	—	—	✓
	Cognition	✓	—	—	✓	—	—	✓	—	—	✓	—	—	✓
	Speech task	✓	✓	✓	✓	✓	✓	✓	✓	✓	✓	✓	✓	✓
	Mood PHQ8^g^ (A^h^)	✓	✓	✓	✓	✓	✓	✓	✓	✓	✓	✓	✓	✓
	Anxiety GAD7^i^ (A or W^j^)	✓	—	—	—	—	—	✓	—	—	—	—	—	✓
	Self-esteem RSES^k^ (A)	✓	—	—	—	—	—	✓	—	—	—	—	—	✓
	Quality-of-life WSAS^l^ (A or W)	✓	—	—	—	—	—	✓	—	—	—	—	—	✓
	BIPQ^m^ (A or W)	✓	—	—	—	—	—	✓	—	—	—	—	—	✓
	Change in medications (T^n^ or F2F^o^)	—	—	✓	—	—	—	✓	—	—	—	—	—	✓
	CSR^p^ (T or F2F)	—	—	✓	—	—	—	✓	—	—	—	—	—	✓
	LTE-Q^q^ (T or F2F)	—	—	✓	—	—	—	✓	—	—	—	—	—	✓

^a^—: Task or assessment not required.

^b^✓: Task or assessment required.

^c^TAM-FF: Technology Assessment Model Fast Form.

^d^PSSUQ: Post-Study System Usability Questionnaire.

^e^RMT: remote measurement technology.

^f^ESM: experience sampling method.

^g^PHQ8: 8-item Patient Health Questionnaire.

^h^A: assessed via app.

^i^GAD7: 7-item Generalized Anxiety Disorder questionnaire.

^j^W: web-based assessment.

^k^RSES: Rosenberg Self-esteem Scale.

^l^WSAS: Work and Social Adjustment Scale.

^m^BIPQ: Brief Illness Perceptions Questionnaire.

^n^T: telephone assessment.

^o^F2F: face to face assessment.

^p^CSRI: Client Service Receipt Inventory.

^q^LTE-Q: List of Threatening Experiences Questionnaire.

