### Study Outcomes

The primary outcome of interest was participants’ acceptability and usability of the RADAR technology, including the wearable, the apps, and the assessment scheme. Acceptability and usability will be evaluated using the Post-Study System Usability Questionnaire (PSSUQ) [46]; the Technology Assessment Model Fast Form (TAM-FF) [47]; and ad hoc created qualitative interviews undertaken at 1, 3, and 6 months postenrollment. Participants who dropped out before the study endpoint will be contacted to complete an interview.

Secondary outcomes include (1) sensitivity and false alarm rate of the device, as compared with patient seizure diary, for different seizure types: generalized tonic-clonic seizures, focal seizures (FS) with motor features, FS with autonomic features, and FS with dyscognitive features and (2) identification of variables influencing the long-term trajectory of seizure frequency: pRMT features (measured through the wearable sensors and smartphone sensors), and aRMT assessments, including comorbidities, seizure precipitants, ESM, speech, and cognitive functions.

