In the general epilepsy population, psychiatric comorbidities are frequent, up to 90% identify the presence of at least one seizure precipitant and many report feelings preceding their seizures, including mood, behavior, and cognitive alterations (premonitory features) [53-55]. The presence of complex interactions between seizure precipitants and premonitory features [56,57] makes the assessment of their real impact on seizure risk variation difficult. In addition, studies performed so far are lacking methodological tools that allow an objective and adequate assessment of precipitants, including a measurement of their sudden variation. In fact, irrespective of their retrospective or prospective design, research studies have surveyed patients with the use of cross-sectional questionnaires and diaries, which are subject to recall bias and lack of time stamps. Another major methodological issue of the current literature data is related to the choice of arbitrary time windows between the assessment of a specific factor and the consequent occurrence of a seizure, usually using the data collected the day before to speculate about their influence on seizures occurring the following day. Prediction might be more robust over short time frames for some precipitants and premonitory features and over long time periods for others. Moreover, it is not clear whether a single report of a status (eg, stress or anxiety) reflects the average over the course of a day [58], and multiple collection points per day might be necessary to take into account symptom fluctuations and variations from day to day or moment to moment.

A complete assessment of seizure occurrence, precipitants, premonitory features, and their interactions cannot leave aside all the aforementioned considerations. RADAR Epilepsy aims to overcome the current methodological issues and to develop an ideal framework of continuous data collection intended to identify ictal and preictal states through the use of aRMT and pRMT. Context-sensitive fine-grained assessments with an excellent temporal resolution in the context of daily life are the hallmarks of RADAR Epilepsy.

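### For seizures before the evening form is completed, its ratings of sleep quality, stress, mood, anxiety and medication compliance are made after the event, so daily models cannot treat them as prospective predictors

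*Protocol article*

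**What the plan says.** Study Technology in the protocol article describes one daily self-report: "Each evening, participants will be prompted to complete a daily assessment to provide self-reported information about medication compliance, sleep quality, alcohol use". The list continues with "menstrual cycle, stress, mood, anxiety, and seizure occurrence. If a seizure is reported, the participant will be automatically directed to an ad hoc created seizure", that is, to a separate diary. On that diary the text says: "Information on clinical symptoms and manifestations, time of the event, and possible precipitants will be collected through the diary". Table 1 shows this questionnaire as daily and lists no morning rating.

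A second route, the experience sampling method (ESM), gathers "real-time self-reported data on mood, stress, cognition, activity, location, social interactions, physical state, and medication use". It is intermittent: once every six weeks, "participants will receive notifications to complete 9 questionnaires per day over a 6-day period". The row "ESM^f^ assessment" in Table 1 is ticked at weeks 0, 6, 12, 18 and 24.

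Study Outcomes names, among the variables to be related to seizure frequency, "aRMT assessments, including comorbidities, seizure precipitants, ESM, speech, and cognitive functions". The Statistical Analysis Plan section models the seizure count per unit of time, with day and week as examples, on each feature. It then builds prediction models in which features aggregated over a period predict the count over the same duration. It also plans change-from-earlier features and wearable-derived information on sleep, activity and mood. The third aim under Study Objectives is prospective estimation of variation in seizure occurrence.

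**The concern.** The candidate precipitants and the outcome are recorded in one sitting. A participant who had a seizure that afternoon rates sleep quality, stress, mood and medication compliance that evening knowing about it. Two distortions follow. The seizure may colour recall of the night, or of whether a dose was taken. Stress, mood and anxiety may also be raised by the seizure, so that the effect runs backwards. A daily model that pairs that form's ratings with that day's count can then show an association for a factor that has no influence on seizures.

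Seizure precipitants are a named part of the second secondary outcome. The Discussion itself faults earlier diary studies for recall bias. Analysis can order ratings against events, but it cannot create a pre-event rating that was never collected.

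**Working it through.** The plan gives no figure on this point to reproduce, so the check is of timing and coverage.

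**1. Order of rating and event.** Let the form be completed at time F and the seizure occur at time S on the same day.
- If S < F, the form's ratings come after the event.
- If S > F, they come before it.

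The clock time of the evening prompt is not given, so the share of seizures with S < F cannot be computed.

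**2. Days with another same-day rating.** Inputs: 24 weeks of follow-up and five ESM ticks (Table 1), with 6 days per period (Study Technology).
- Follow-up: 24 × 7 = 168 days.
- Five periods: 5 × 6 = 30 days; 30/168 = 17.9%.
- Four periods, if the week-24 period falls outside follow-up: 4 × 6 = 24 days; 24/168 = 14.3%.
- Evening form only: 168 − 30 = 138 days (82.1%) to 168 − 24 = 144 days (85.7%).

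Sleep quality is not among the listed ESM contents, so the evening form is its only listed self-report on all 168 days. The two-weekly mood questionnaire has 13 ticks. Even if all 13 fell outside ESM days, mood would be covered on 30 + 13 = 43 of 168 days (25.6%), with nothing added for sleep quality or medication compliance.

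**3. Seizures involved.** Inputs: 32 participants and at least 2 seizures per month (Study Design and Population), over 6 months. Assumptions: everyone at the minimum rate, even spread, no dropout.
- Total: 32 × 2 × 6 = 384.
- On ESM days: 384 × 24/168 = 55 to 384 × 30/168 = 69.
- On other days: 384 − 69 = 315 to 384 − 55 = 329.

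Only the part of these 315 to 329 with S < F is affected.

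**4. Effect of the time unit.** Let δ be the shift in a rating, in daily SDs, caused by knowing of a seizure. For a factor with no true effect:
- Daily model: the spurious difference is δ.
- Weekly mean with one affected day: δ/7 daily SDs.
- Monthly mean with two affected days in 30: 2δ/30 = δ/15 daily SDs.

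The document gives no value for δ. If δ were 0.3 to 0.5 (an assumption), the weekly shift would be 0.04 to 0.07 and the monthly shift 0.02 to 0.03. The daily figure would merely return the assumption.

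**5. What the other sources supply before a daytime seizure.**
- Previous evening's form: stress, mood, anxiety, alcohol and the previous day's medication. It cannot contain the night in between or that day's doses.
- Wearable: sleep information without recall. No listed sensor records medication intake.
- Change features: a change from the previous time point still contains the current, possibly post-event, rating.

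**The case against.** Much can be said for the plan.

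- **Ratings often precede seizures.** A reader might infer that precipitants are always recorded after the event. The document does not support that. An evening rating precedes any seizure later that evening, overnight or the next day, and the diary records event time, so ratings and events can be ordered. This stands and limits the point to seizures before the form.
- **Sleep is measured passively.** The wearable is to be worn throughout and is to yield sleep information. This stands for sleep as such. It does not replace the self-rated item or cover medication compliance.
- **The sleep item's reference period is not stated.** The text says sleep quality, not last night's sleep. The latter is the natural reading of a daily item but remains an inference. Item wording and prompt time may well be in the full protocol.
- **The Discussion does not reject lagging.** It gives the day-before window ("usually using the data collected the day before to speculate about their influence on seizures occurring the following day") as the usual example of an arbitrary choice, and allows that longer periods may suit some factors. The reading that lagged evening ratings would be exactly the design it criticises is too strong. So is the claim that the study simply repeats earlier flaws, given event times, ESM and passive sensing.
- **The same duration may mean equal length.** If the authors intend a preceding window of equal length, the models are sounder than they look. The text does not say so, and no lag is stated for the univariate step.
- **Weekly models are diluted.** This stands (working, step 4), and the secondary outcome concerns long-term trajectory. Daily models are nevertheless named as an option.

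**Conclusion.** The point holds in limited form. For a seizure before the evening form is completed, that form's precipitant ratings are outcome-aware. On 82% to 86% of days no other same-day self-report is scheduled beyond the widely spaced scales, and for sleep quality none is listed on any day. Daily associations built on these ratings are concurrent, not prospective as aim 3 requires.

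The number of affected seizures and the size of the bias cannot be derived from the document. The first needs the prompt time and the time-of-day distribution of seizures; the second needs δ. Coverage rests on Table 1 being complete for daily self-reports. The matter concerns one data stream in a secondary analysis and does not touch the primary acceptability and usability outcome.

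**What to change.** 1. **Collection.** Move the sleep-quality item to a short morning prompt, with one current rating each of stress, mood and anxiety. Leave the other items in the evening form. Study Monitoring already allows changes to the questionnaire schedule. As enrolment has begun, record the date of the change.
2. **Daily models.** Use only ratings completed before the recorded event time, by one rule for seizure and seizure-free days alike: the morning rating, or the previous evening's rating, for every day. Excluding evening ratings only on seizure days would make the use of data depend on the outcome.
3. **Overnight seizures.** Use wearable-derived sleep, since a morning sleep rating would again be made knowing of the seizure. Define its window identically for nights with and without a seizure, because the seizure itself may disturb the recording.
4. **Reporting.** Present same-evening ratings as concurrent associations on all days, not as predictors. State whether the same duration means the same interval or a preceding one of equal length.

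The cost is one brief extra prompt each day for six months. That is a real burden in a study whose primary outcome includes acceptability of the assessment scheme, and which already sends nine prompts a day in ESM periods. Medication compliance would still have a pre-event rating only from the previous evening or ESM. If the prompt is not accepted, items 2 to 4 should still be applied, using the previous evening's ratings; they need no new data.
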